### Recruitment and study participants

Eight government public primary schools from the Hunter Region, NSW, Australia will be recruited to participate in the EASY minds RCT. Stage 3 classes (Grades 5 and 6) at the study schools will be invited to participate in the study. School principals will receive an initial letter followed by an email. Schools will be randomly selected from a list of primary schools within a 20 km radius from the University of Newcastle. Schools will then be matched on size and demographics using the participating schools index of community socio-educational advantage (ICSEA). The ICSEA value is determined based on family background information provided to schools directly by families and includes data relating to parental occupation, and the school education and non-school education levels they achieved.

Randomization will occur after baseline assessments. A simple computer algorithm will be used to randomly allocate schools to either control or the treatment conditions by an independent researcher not involved in the study. This method will ensure all schools have an equal likelihood of allocation into one of the two study arms. Trained research assistants will conduct all assessments and administer all student questionnaires. All researchers will complete training sessions prior to assessment to maintain consistency and where possible, the same assessors will be used at baseline and post-test. Figure 1 shows the flow of participants through the study.

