**Flow of participants through the EASY Minds study**

### Sample size calculation

Power calculations were conducted to determine the sample size required to detect changes in the in the primary outcome of accelerometer-determined physical activity counts per minute (CPM) [27]. Calculations assumed baseline-posttest correlation scores of *r* = 0.30 and were based on 80% power, with alpha levels set at *p* < 0.05. Using the standard deviation (SD) of change observed in the EASY Minds pilot study (SD =200 CPM) and a conservative intra-class correlation coefficient (ICC = 0.15), it was calculated that a study sample of N = 200, with 8 clusters (i.e., schools) of 25 students would provide adequate power to detect a between group difference of 200 CPM across the school day.

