### Statistical methods

Statistical analysis of both the primary and secondary outcomes will be conducted with linear mixed models using SPSS statistics version 20 and alpha levels will be set at *p* > 0.05.

The models will be used to assess the impact of treatment (EASY Minds or control), time (baseline and post-test) and the group-by-time interaction, these three terms forming the base model. The models will be specified to adjust for the clustered nature of the data and will include all randomized participants in the analysis. Mixed models are robust to the biases of missing data and provide appropriate balance of Type 1 and Type 2 errors [43]. Mixed model analyses are consistent with the intention-to-treat principle, assuming the data are missing at random [44]. Sex and weight status (based on body mass index) will be included as covariates in the models. Further sub group analysis will be conducted based on sex, weight status, mathematical ability, and enjoyment of mathematics and on-task behaviour.

The focus groups and interviews will be digitally recorded with the participants’ consent and transcribed verbatim. A computer program (NVIVO 10) will be used to assist with the organisational aspects of data analysis. Analysis will be conducted by an independent qualitative researcher. Analysis will be performed using a standard general inductive approach to qualitative analysis. Initially, inductively derived codes or labels will, be formulated from the meaning units arising from the data. The developing coding scheme will be continually revised and further expanded after coding of additional transcripts. Following coding of all the transcripts, emerging themes will be identified and defined.

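### The planned group-by-time test is a change-score contrast; at the plan's r = 0.30, if that value holds for students and schools alike, adjusting for the student's baseline gives 35% lower variance

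*Protocol article*

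**What the plan says.** Under Statistical methods, the protocol article analyses primary and secondary outcomes with linear mixed models. The base terms are treatment, "time (baseline and post-test) and the group-by-time interaction, these three terms forming the base model". The models adjust for clustering, include all randomised participants, and carry sex and weight status as covariates. The baseline value of the outcome is not listed as a covariate. It enters as an outcome at the first time point, and nothing constrains the arms to a common baseline mean.

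Under Sample size calculation: "Calculations assumed baseline-posttest correlation scores of *r* = 0.30 and were based on 80% power", "with alpha levels set at *p* < 0.05". The SD is described thus: "Using the standard deviation (SD) of change observed in the EASY Minds pilot study (SD =200 CPM". Clustering enters through "a conservative intra-class correlation coefficient (ICC = 0.15", and the design is "a study sample of N = 200, with 8 clusters (i.e., schools) of 25 students". The target difference is 200 CPM across the school day. One correlation is given, without saying whether it applies to students, schools or both.

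Under Recruitment and study participants: "Randomization will occur after baseline assessments".

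**The concern.** Because baseline is measured before allocation, the two arms have the same expected baseline. The group main effect therefore estimates only chance imbalance. Leaving it free turns the interaction into a comparison of mean changes, which subtracts the whole baseline value. At a low correlation, subtracting a noisy baseline can add more variance than it removes. Regression on baseline subtracts only the predictive part.

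At stake is precision in a trial of eight schools, where the effect is judged on about 6 between-school degrees of freedom. The trial collects a school week of baseline accelerometry in every school, and how that measurement is used affects whether the stated 80% power is reached.

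**Working it through.** **Inputs.** From Sample size calculation: r = 0.30, SD 200 CPM, ICC 0.15, 8 schools of 25, difference 200 CPM, 80% power, alpha 0.05 (taken as two-sided; the protocol does not say). From the abstract: 4 schools per arm, hence 100 students per arm and 8 − 2 = 6 between-school degrees of freedom. Design effect: 1 + 24 × 0.15 = 4.6.

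**The plan's own figure.** Total N by normal approximation = 4 × (1.96 + 0.8416)² × 4.6 × v × (200/200)² = 144.4v, where v is the variance factor.
- SD 200 as a single-time SD, v = 2(1 − r) = 1.40: N = 202, power 79.6% at N = 200. This reproduces the stated N = 200.
- SD 200 as the SD of change, v = 1: N = 144, power 90.9% at N = 200. On t with 6 df the power is 78.4%, close to the stated 80%.

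Either way the trial appears to be sized on change. Both readings of the SD are carried forward.

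**What the interaction estimates.** With complete data it is the difference between arms in mean (post − baseline). Covariates constant over time, such as sex and weight status, drop out of it.

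**Variance factors with r = 0.30 at both levels** (units of the single-time variance):
- change: 2(1 − 0.30) = 1.40
- post-test only: 1.00
- baseline-adjusted: 1 − 0.30² = 0.91
- ratio: 0.91/1.40 = 0.65, so 35% less variance; the planned standard error is √(1/0.65) = 1.24 times the adjusted one.

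**Power for 200 CPM.** SE = SD × √(2 × 4.6 × v/100); noncentral t, 6 df. Under the second reading the single-time SD is 200/√1.40 = 169.

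| Reading of SD 200 | Change: SE, power | Baseline-adjusted: SE, power |
|---|---|---|
| Single-time SD | 71.8, 64.4% | 57.9, 82.0% |
| SD of change | 60.7, 78.4% | 48.9, 92.3% |

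Simulation of nested normal data under the first reading agrees: about 64–65% against 82%, with type I error about 5% for the student-level baseline covariate.

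**Dependence on the school-level correlation.** The protocol does not give this value; call it rc. In a school mean, 25 × 0.15/4.6 = 82% of the variance lies between schools, so rc dominates. Holding the overall r at 0.30:
- student-level correlation: rs = (0.30 − 0.15rc)/0.85
- correlation of school means: R = (3.6rc + 0.30)/4.6
- change factor: 2(1 − R)
- adjusted factor, with the student-level slope: 1 + rs² − 2·rs·R

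Power below uses the single-time SD of 200.

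| rc | R | Change | Adjusted | Variance cut | Power, change to adjusted |
|---|---|---|---|---|---|
| 0 | 0.07 | 1.87 | 1.08 | 42% | 53% to 75% |
| 0.3 | 0.30 | 1.40 | 0.91 | 35% | 64% to 82% |
| 0.5 | 0.46 | 1.09 | 0.83 | 24% | 75% to 85% |
| 0.6 | 0.53 | 0.93 | 0.80 | 14% | 81% to 87% |
| 0.7 | 0.61 | 0.77 | 0.77 | 0% | 88% to 88% |
| 0.8 | 0.69 | 0.62 | 0.75 | −22% | 93% to 88% |

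Holding the student-level correlation at 0.30 instead gives nearly the same break-even: 1.09 − 0.6R = 2 − 2R at R = 0.65, that is rc = (0.65 × 4.6 − 0.255)/3.75 = 0.73. At rc = 0.8 power then goes from about 94% to 92%.

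Change is less precise than post-test only when R < 0.5, that is rc < (2.3 − 0.30)/3.6 = 0.56.

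**The case against.** The strongest reply is that nothing here is an error. A group-by-time mixed model is a standard and valid analysis, the change estimator is unbiased under randomisation, and the stated N = 200 reproduces with the change factor of 1.40, so planning and analysis agree. All of that stands. It limits the point to efficiency, but it does not remove it: the model is explicitly fixed, and the inefficiency follows from the plan's own r if that value holds at both levels.

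Second, the size rests on a school-level correlation that the protocol does not state. This also stands. A reader might infer that 35% is guaranteed, or that the planned test is always worse than ignoring baseline. The documents support neither, because both need the school means to correlate weakly.

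Third, adjustment has a price. With stable school means the student-level slope loses precision, and a plain covariate drops students without a valid baseline although the protocol promises to include all randomised participants. So baseline adjustment should not be presented as free.

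Fourth, a reader might prefer a model with a common baseline mean and separate school-level covariances, expecting it to give the full gain whatever the school-level correlation. With eight schools it does not. In balanced data it behaves essentially like regression on school means with a slope fitted to eight points. In simulation at a school-level correlation of 0.30, such a slope cut variance by only about 20% (power about 71–72%), and at 0.8 it was slightly worse than change. Model-based type I error for the constrained model was 7.1% to 9.3% on 6 df. That objection holds, and it decides which remedy to recommend.

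**Conclusion.** The point holds as a conditional efficiency weakness. The planned test is valid and consistent with its own sample size basis. If r = 0.30 describes both students and schools, the planned contrast carries a variance factor of 1.40 where 0.91 is available. Adjusting for the student's baseline then raises power from about 64% to 82%, or from 78% to 92%, depending on how the SD of 200 is read. Under either reading, the planned test falls short of 80% on 6 df and the adjusted one exceeds it.

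The result assumes 8 schools of 25, ICC 0.15, complete data and normal outcomes. The gain is about 14% of variance at a school-level correlation of 0.6 and nil near 0.7. At 0.8, power falls from about 93–94% to 88–92%. The figures are for CPM, the only outcome for which the protocol gives these inputs. The change is worth making, but the trial's validity does not depend on it.

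**What to change.** In Statistical methods, define the primary analysis as a linear mixed model of the post-test value on treatment, with the student's baseline value, sex and weight status as covariates and a random school effect. Test treatment with between-school (small-sample) degrees of freedom. State how students without a valid baseline are kept, for example by mean imputation of the baseline covariate with a missing indicator. Report the group-by-time model as a sensitivity analysis, and use the same model for the other outcomes measured at both times.

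The cost is a few sentences and no extra data. There are two downsides: some loss of precision if school means prove very stable over time, and an explicit rule for missing values. Students with a baseline but no post-test add nothing to this model, so the statement that all randomised participants are included needs matching wording; the sensitivity analysis retains them.

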### Physical activity

The primary outcome will be children’s school-based PA levels. Actigraph accelerometers (GT3X, Pensacola, USA) will be used to provide an objective measure of both PA intensity and duration [30]. The Actigraph accelerometer has acceptable reliability and validity in both children and adolescents [31]. Accelerometers will be worn Monday through to Friday, during school hours only. This will vary slightly for each school setting as the schools are likely to have different start and finish times. The classroom teachers will receive training in how to instruct students to wear accelerometers and be responsible for distributing and collecting the accelerometers on a daily basis. Accelerometers will be attached to an adjustable elastic belt and worn on the right hip. Raw data from the accelerometer will be screened and analysed using Meter plus software version 4.7 which allows for time specific analysis to accurately analyse lesson- and school-time PA. Participants’ PA will be included for analysis if they wear the accelerometer for at least five school hours on any given day. Similarly, students will only be included in the analysis if they wear the accelerometer for 50 minutes of the 60 minute mathematic lessons. This time period may vary from school to school as a result of schools individual timetables. The Evenson cut-points will be used to classify activity as sedentary: (0–100 CPM, light (101–2295 CPM), moderate (2296–4011 CPM), vigorous 4012 - ∞ CPM ) or MVPA [32]. MVPA is a variable calculated by summing moderate and vigorous PA. Data will be collected in 15 second epochs and non-wear time will be defined as 20 minutes of consecutive zero’s [33].

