#### Mathematic achievement

Mathematics achievement will be measured using a Mathematics Progressive Achievement Test (PAT) [39]. For the purpose of this study cohort, PAT version 3 will be used. The PAT Mathematics test has 37 questions and takes 40 minutes to administer. The test will be administered by the classroom teacher under exam conditions as recommended by the Australian Curriculum for Educational Research (ACER). The 37 questions form separate items for individual mathematics sub-strands. These being number (n = 14), Space (n==6), Measurement (n = 6), Data (n = 5) and Number (no calculator) (n = 6). The test will provide evidence of student’s strengths and weaknesses and change over time.

Demographic information (i.e., age, sex, language, country of birth) will be collected at baseline via questionnaire alongside questionnaires of children’s preferred learning styles and intelligence strengths. These will be used to profile the children recruited in the study. Learning styles will be measured using the Barsch Learning Style Reference Form [40] and students’ preferred perceptual modality will be determined. Preferred perceptual modality (learning style) has been defined as the conditions under which individuals concentrate process and internalise information [41]. The Barsch learning style reference form defines three perceptual modalities. These are kinaesthetic (relating to body movement), visual (relating to the eyes) and auditory (relating to the ears). Students’ intelligence strengths will be assessed using a Multiple Intelligences Checklist for Upper Primary and Secondary (MICUPS) [42].

Weight will be measured in light clothing without shoes using a portable digital scale (Seca 770, Wedderburn) to the nearest 0.1 kg and height will be measured to the nearest 0.1 cm using a portable stadiometer (Design No. 1013522, Surgical and Medical Products, Seven Hills, Australia). Height, weight, learning style and intelligence strengths will only be measured at baseline to profile the sample. No measures will be taken at follow up.

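### Sex and weight status, entered as time-constant covariates, drop out of the group-by-time estimate for every child with both measurements; a baseline-adjusted post-test model would let them act and be more precise

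*Protocol article*

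**What the plan says.** The Statistical methods section builds the linear mixed model from treatment, "time (baseline and post-test) and the group-by-time interaction, these three terms forming the base model". It then says "Sex and weight status (based on body mass index) will be included as covariates in the models". No covariate-by-time term is mentioned. The section on mathematics achievement states that "Height, weight, learning style and intelligence strengths will only be measured at baseline to profile the sample", so weight status has one value per child, as sex does.

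On who is analysed, Statistical methods says "The models will be specified to adjust for the clustered nature of the data and will include all randomized participants in the analysis", and adds that "Mixed model analyses are consistent with the intention-to-treat principle, assuming the data are missing at random". The Physical activity section sets wear rules that will leave some outcomes missing. School-day data "will be included for analysis if they wear the accelerometer for at least five school hours on any given day", and for lessons "students will only be included in the analysis if they wear the accelerometer for 50 minutes of the 60 minute mathematic lessons".

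The Recruitment section places randomisation after baseline assessment. The sample size section uses a baseline to post-test correlation of 0.30, an SD of change of 200 CPM, an ICC of 0.15, 8 schools of 25 children, 80% power and a target difference of 200 CPM.

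**The concern.** With two waves, group-by-time is the difference between arms in within-child change. A variable that adds the same amount to a child's baseline and post-test values cannot alter that change. A reader who sees sex and weight status listed as covariates will probably take the intervention effect to be adjusted for them. For children with both waves, it is not.

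In a trial of 4 against 4 schools, a chance difference between arms in sex or weight status is plausible. If that variable is related to change over the term, the planned terms leave the difference where it is. The model also uses the baseline value only through a change contrast, which is a costly use of it when the baseline to post-test correlation is as low as 0.30.

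**Working it through.** **Reproducing the plan's figure.** The design effect is 1 + (25 − 1) × 0.15 = 4.6. With SD 200 and difference 200, the usual normal formula (two-sided 5% assumed, 80% power) needs 16 children per arm before clustering, so 2 × 16 × 4.6 = 147 children. The standard error with 200 children is 200 × √(4 × 4.6 / 200) = 60.7 CPM. Power at 200 CPM is 90.9% on the normal distribution and 78.4% on a t distribution with 8 − 2 = 6 degrees of freedom (detectable difference 203.4 CPM). The stated 80% is reproduced closely enough and is not in dispute.

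**Algebra.** Write the model for child *i* at wave *t* as Y = a + b1·G + b2·T + b3·G·T + c1·Sex + c2·Weight status + random effects + error. Subtracting baseline from post-test gives b2 + b3·G + error. Neither c1 nor c2 remains, so the estimate of b3 from complete pairs does not depend on them. They do act on b1, which in this model is the arm difference at baseline and not the effect of interest.

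**Simulation.** I simulated 8 schools × 25 children × 2 waves with school, school-by-time and child effects. Variances, covariate effects and missingness rates are my assumptions. There were 60 trials per setting.

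| Setting | Mean absolute difference, with v without covariates | Largest | Mean SE without / with |
|---|---|---|---|
| Complete data | 0.000 CPM | 0.00 | 33.96 / 33.95 |
| 10% missing at random | 2.2 CPM | 6.6 | 36.86 / 36.85 |
| 20% missing at random | 2.7 CPM | 11.5 | 39.84 / 39.68 |
| Missingness depends on sex in one arm | 9.0 CPM | 18.7 | 39.56 / 39.54 |

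In the last row the mean estimate was 192.0 without the covariates and 201.0 with them, against a true 200. The Monte Carlo error of each mean is about 39.6/√60 = 5.1, so the paired shift of 9 CPM is firmer than either mean.

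In one complete trial fitted with a school intercept only, the estimate was 175.64 both ways, but the standard error went from 34.49 to 32.47. Adding covariate-by-time terms moved the estimate to 170.71.

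**Size of an uncorrected imbalance.** Assume a 10 to 20 point arm difference in the share of girls and a sex difference in change of 50 to 100 CPM. Then 0.10 × 50 = 5 to 0.20 × 100 = 20 CPM stays uncorrected. That is 2.5 to 10% of the 200 CPM target and at most about a third of the 60.7 CPM standard error.

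**What baseline adjustment gives.** If the SD of change is σ√(2(1 − r)), then σ = 200/√1.4 = 169.0. The residual SD of the post-test given baseline is σ√(1 − r²) = 169.0 × √0.91 = 161.3. With the same design effect, the standard error is 161.3 × √(4 × 4.6 / 200) = 48.9 CPM. The ratio to the change analysis is √((1 + r)/2) = √0.65 = 0.806, so the detectable difference on 6 degrees of freedom falls from 203.4 to about 164 CPM. With the SD of change held at 200, r = 0.5 gives 60.7 × 0.866 = 52.5 and r = 0.7 gives 60.7 × 0.922 = 55.9. In a separate simulation, adding covariate-by-time terms to the planned model without baseline adjustment gained almost nothing (60.8 to 60.7).

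**Children without a weight.** A child with no covariate value has no fitted mean, so it cannot enter the likelihood unless the value is imputed or given its own category. If 5 to 10% were unweighed (assumption) and left out, 10 to 20 of 200 children would be lost and the standard error would rise from 60.7 to 61.0–61.3 CPM, about 1% at most.

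**The case against.** A reader might infer three stronger things that the documents do not support.

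- *The adjusted result always equals the unadjusted one.* This is exact only for complete pairs. The wear rules make incomplete pairs likely, and the estimates then differ.
- *Weight status can only cost children.* Covariates that predict both the outcome and its missingness make missing at random more plausible. The simulation showed this with sex, and weight status would work the same way if it predicts missing wear. The protocol does not say how a missing weight is handled, nor that such children are dropped; loss of those children and the 5 to 10% share are assumptions.
- *The trial is biased.* Under randomisation, a chance imbalance does not bias the estimator or invalidate the test, and the article never says the covariates are there to correct one.

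It can also fairly be said that a condensed article may leave covariate-by-time terms, random effects and missing covariates to an analysis plan. That stands for missing covariates and random effects, and the latter matter because the standard error can move under a school-intercept model. It stands less well for the model terms. The article lists these and adds the two variables simply as covariates, for which main effects are the natural reading. If an analysis plan does add the time interactions, the cancellation no longer applies, but the precision argument for baseline adjustment remains. The planned subgroup analyses by sex and weight status would examine differential change, but they do not adjust the main estimate.

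**Conclusion.** The point holds as one of efficiency and clarity. For children with both waves, sex and weight status as main effects leave the group-by-time estimate untouched. Their only influence on it is through incomplete pairs, where it is modest: about 2 to 3 CPM on average under random missingness, and about 9 CPM in the sex-dependent scenario.

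The planned analysis is valid. A better one is available at little cost, with a standard error about 19% smaller (48.9 against 60.7 CPM). That figure rests on r = 0.30, on reading 200 CPM as the SD of change, and on the same ICC of 0.15 applying to the baseline-adjusted residuals. It is due to the baseline term. The documents give no figure from which to size any further gain from sex or weight status.

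**What to change.** In Statistical methods, state that the treatment effect is estimated from the post-test value, adjusted for the child's own baseline value, sex and weight status, with school clustering in the model. Equivalently, use a mixed model over both waves with a common baseline mean for the two arms and with covariate-by-time terms. This form keeps children with one wave, and it is justified because randomisation follows the baseline assessment.

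Keep children without a weight measurement, for example through a not-measured category of weight status, or leave weight status to description and the planned subgroups. The statement that the models "will include all randomized participants in the analysis" then holds for this covariate.

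The cost is slightly more analysis wording, a recoded variable and a few child-level degrees of freedom. A plain post-test model also drops children with one wave, or must impute for them, which favours the constrained-baseline form. Adding covariate-by-time terms to the present model would make the adjustment real but is not expected to gain noticeable precision.
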